### Sample size

We hypothesize that the effect of low-dose AM at 12 weeks is non-inferior to the golden standard CBT-I. A low-dose AM will be considered non-inferior to CBT if the mean post treatment ISI total score does not exceed that of the CBT-I group by more than 4 points, i.e., 50% of the minimum clinical significant difference reported following CBT-I. The standard deviation of the ISI in our study is assumed 4.4 [61]. Sample size determination following the recommendations outlined in Tamayo-Sarver et al. [62] using a one-tailed test and a 5% significance level showed that 84 participants in each group will provide adequate power (90%) to reject the null hypothesis that the ISI change produced by low-dose amitriptyline is not similar to those produced by CBT-I. The dropout rate is estimated to be 13% [41]. Hence, 190 participants in total will be included.

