### Statistical analysis

Demographic and clinical characteristics (e.g., age, gender, medical condition, preference and type of insomnia) and primary and secondary outcomes at baseline (e.g., sleep efficiency, emotional complaints) will be presented in means (standard deviations) and numbers (percentages) depending on their distribution.

The null hypothesis states that there is a difference in mean scores on the primary outcome between the treatment groups; the alternative hypothesis is that the difference in mean scores on the primary outcome measure does not differ by more than the non-inferiority margin. The primary analysis will be conducted according to intention-to-treat, i.e., all randomized patients are included and are analyzed in their randomly assigned treatment group. Outcomes that are based on measurements at multiple time points, i.e., weeks 6 and 12, are analyzed using mixed linear models. Mixed linear models can handle the presence of missing data without the need for imputation and still provide valid estimates of treatment effects.

The primary outcome for analysis is the mean subjective insomnia severity as assessed using the ISI at week 12. To test for the difference between the two treatment groups, the primary outcome of ISI score at week 12 will be analyzed using analysis of covariance (ANCOVA) with treatment group (amitriptyline or CBT-I) as the independent variable and the baseline value as a covariate. We will check for violations of necessary assumptions of ANCOVA (normality, homogeneity of variance and random independent samples). We will calculate a one-sided 95% confidence interval around the mean difference in the primary outcome between the treatment groups to determine if the upper limit of the confidence interval will be below the non-inferiority margin of 4 points. Amitriptyline will be declared non-inferior to CBT-I if the upper bound of the 95% confidence interval does not exceed the non-inferiority margin of 4 points. If amitriptyline is shown to be non-inferior, we then will proceed to superiority hypothesis testing. For superiority testing, we will consider the two sided 95% confidence interval of the mean difference between both groups on the primary outcome as established in the ANCOVA and verify if it includes zero or not.

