The primary analysis will be conducted according to intention-to-treat, i.e., all randomized patients are included and are analyzed in their randomly assigned treatment group. We will use multiple imputations to handle missing data for outcomes that are based on the measurement at a single time point, including the primary outcome of the ISI score at week 12. We will include all baseline demographic and clinical characteristics in the imputation model. We will impute a total of five datasets and these will be pooled according to Rubin’s rule [63].

Additionally, the mean ISI score over time will be compared between the two treatment groups using linear mixed models with treatment group (amitriptyline or CBT-I) and time (6 and 12 weeks from baseline) included as fixed effects and ISI score at baseline included as covariate.

We will repeat the ANCOVA and the linear mixed models analysis of the ISI score as a per protocol analysis in which only patients who actually received their assigned treatment (in the CBT-I group attendance of at least 5 out of 7 sessions and in the AM group at least 70 out of 84 days medication) will be included.

Percentages responders until relapse at 2, 4, 6, 8, 10, and 12 months post treatment in both treatment groups will be compared using survival analyses. We will express the difference between amitriptyline and CBT-I in effect sizes and percentage responders. Treatment response is defined as ≥ 8 point reduction on ISI. A relapse is defined as a drawback of ≤ 8 points to the baseline score of the Insomnia Severity Index measured during follow-up at two subsequent measurements.

ANCOVA will be repeated on the secondary outcome measures assessed at week 12 and 12 months, adjusted for the baseline measurement and the linear mixed models will be repeated for the secondary outcomes sleep quality, fatigue, emotional complaints, physical functioning, impairment of functioning, and pain, all assessed at weeks 6 and 12 and 12 months post treatment adjusted for the baseline measurement, according to intention to treat and per protocol analyses. Bonferroni corrections will be applied to the p-values to account for multiple comparisons.

Rates of reported side effects, withdrawal, and rebound symptoms as well as the treatment evaluation items will be described.

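### Five imputations for the week-12 ISI is valid but low: it adds avoidable seed-to-seed noise that matters mainly for a borderline superiority result, not for the expected non-inferiority verdict

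*Protocol article*

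**What the plan says.** All the relevant text is in the Sample size and Statistical analysis sections of the protocol article.

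- **Number of imputations.** "We will impute a total of five datasets and these will be pooled" using Rubin's rule. This covers outcomes measured at a single time point, "including the primary outcome of the ISI score at week 12".
- **Imputation model.** "We will include all baseline demographic and clinical characteristics in the imputation model".
- **Primary analysis.** The week-12 ISI "will be analyzed using analysis of covariance (ANCOVA) with treatment group (amitriptyline or CBT-I) as the independent variable and the baseline value as a covariate".
- **Non-inferiority.** Amitriptyline passes if its mean "does not exceed that of the CBT-I group by more than 4 points". This is judged by the upper limit of a one-sided 95% interval.
- **Superiority.** If non-inferiority is shown, the plan takes the two-sided 95% interval from the same ANCOVA and will "verify if it includes zero or not".
- **Planning values.** "The standard deviation of the ISI in our study is assumed 4.4", and "The dropout rate is estimated to be 13" percent. The total is 190 patients, allocated 1:1.

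The article gives no reason for choosing five. It also plans a linear mixed model of the ISI at weeks 6 and 12, which needs no imputation, but as an additional analysis and not the primary one.

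**The concern.** Multiple imputation draws random values. With a finite number of imputed datasets, the pooled estimate, its standard error and its confidence limits change if the same data are imputed again with another seed. Both primary conclusions are yes/no readings of a confidence limit, against 4 points and against zero. If the noise is large relative to the distance between the limit and its threshold, the conclusion depends partly on the seed. The question is how large the noise is with five imputations, and which conclusions it can reach. The number is stated for the confirmatory analysis, so this is not a detail left open for the analysis plan.

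**Working it through.** **Inputs from the article:** 95 per arm (190 at 1:1), SD 4.4, margin 4, five imputations, 13% dropout. **Assumptions:** the dropout rate equals the share of missing week-12 ISI; data are missing completely at random; the baseline to week-12 correlation is 0.3 or 0.5. Differences are amitriptyline minus CBT-I, so negative values favour amitriptyline.

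**The plan's own figure.** The article states no Monte Carlo error, so there is none to reproduce. Its sample size is the only related figure. From n = 2·SD²·(1.645 + 1.282)²/d², a distance d = 4 gives 2 × 19.36 × 8.567/16 = 20.7, or 21 per arm, not the stated 84. A distance of 2 gives 82.9, or 83. The total follows as 168 × 1.13 = 190. The check below uses the planned 190 directly.

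**Step 1, analytic size.** With fraction of missing information f and m imputations, the seed-to-seed SD of the pooled estimate is about SE·√(f/m).

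- Complete-data SE, ignoring the baseline covariate: 4.4 × √(2/95) = 0.638.
- With f = 0.13: SE = 0.638/√0.87 = 0.684.
- m = 5: 0.684 × √(0.13/5) = 0.110, about one sixth of the SE.
- m = 50: 0.684 × √(0.13/50) = 0.035.

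**Step 2, simulation of the bound.** This used normal-model imputation, ANCOVA on baseline, Rubin pooling and small-sample degrees of freedom, re-imputing each simulated trial with many seeds. The pooled SE was about 0.60 to 0.66 at 13% missing. The bound is noisier than the estimate because the between-imputation variance is itself estimated from only five values. Ranges in the table span the two correlations.

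| Missing | SD of bound, m = 5 | 95% seed range, m = 5 | SD of bound, m = 50 | 95% seed range, m = 50 |
|---|---|---|---|---|
| 13% | 0.11–0.12 | 0.43–0.48 | 0.03–0.04 | 0.13–0.14 |
| 20% (assumed) | 0.16–0.18 | 0.62–0.68 | 0.05 | 0.17–0.19 |
| 30% (assumed) | 0.24–0.26 | 0.93–1.00 | 0.06–0.07 | 0.23–0.26 |

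**Step 3, effect on the two decisions** (13% missing, correlation 0.5, 200 simulated trials per cell). If a share w of seeds gives a positive verdict in one trial, two seeds disagree with probability 2w(1 − w). The table averages this over trials.

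| Decision | True difference | m = 5 | m = 50 |
|---|---|---|---|
| Non-inferiority | 0 or 1 | 0% | 0% |
| | 2 | 1.7% | 0.5% |
| | 2.5 | 4.9% | 1.1% |
| | 3 | 7.6% | 3.7% |
| Superiority | 0 | 2.0% | 0.5% |
| | -1 | 8.2% | 1.2% |
| | -1.5 | 8.4% | 2.4% |
| | -2 | 3.4% | 1.2% |

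A second simulation with the same planning values gave about 7% for non-inferiority near 2.5. For superiority at -1.5 it gave about 8% with five imputations and about 1% with 50. The individual cells are therefore good to a few percentage points only.

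The non-inferiority rows are as expected. At a true difference of 0 the bound averages about 1, which is 3 points below the margin, and 3/0.12 = 25 seed SDs.

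**Step 4, a borderline p-value.** For data with a two-sided p near 0.05 at 13% missing, the 95% seed range of p is 0.021 to 0.118 with m = 5 and 0.038 to 0.064 with m = 50.

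**The case against.** The strongest reply is that five imputations are statistically sound. Rubin's rules add the (1 + 1/m) between-imputation term and reduce the degrees of freedom, so the estimate is not biased and the interval remains valid. The efficiency loss is about 0.13/5 = 2.6% in variance, or √1.026 − 1 = 1.3% in the SE. This stands: the defect is one of reproducibility.

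Second, a reader might infer that the non-inferiority verdict, the trial's primary objective, is exposed to the seed. Under the plan's figures it is not. No seed changed it at a true difference of 0 or 1. Disagreement appears only from about 2 points, where amitriptyline is truly worse and the bound lies near 4. One caveat applies: the stated 84 per arm matches a 2-point distance to the margin. If the working margin were 2, seed noise would matter more for non-inferiority.

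Third, a reader might suppose that p-values decide the primary tests. They do not: both are read from confidence limits, and the Bonferroni-adjusted p-values belong to the secondary outcomes. The p range in Step 4 is also a selected worst case, since it starts from data near 0.05. The disagreement rates in Step 3 are the fairer summary.

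Fourth, the inputs are approximate. Dropout is not the same as a missing week-12 ISI, and the planned imputation model is richer than the simulated one. A run with 15 uninformative covariates added changed little. The 20% and 30% rows have no support in the article. Whether five imputations govern the 12-month ANCOVAs is an inference, because the secondary outcomes also have mixed models that need no imputation.

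Finally, the absence of a stated random seed is not a finding. That is a programming detail that may sit in an analysis plan not shown here.

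**Conclusion.** The point holds as a minor one. Five imputations are valid but leave avoidable noise: a between-seed SD of about 0.11 to 0.12 ISI points in the one-sided bound, against about 0.03 with 50. The main consequence is for a borderline superiority conclusion, where two seeds disagree in about 8% of trials at true differences of -1 to -1.5, against about 1 to 2% with 50 imputations. Borderline secondary ANCOVA p-values are affected in the same way where imputation applies. The non-inferiority verdict is effectively independent of the seed unless the bound lies close to 4. These sizes rest on 13% of week-12 ISI scores missing completely at random, SD 4.4, 190 patients and an assumed baseline correlation of 0.3 to 0.5 (0.5 for the disagreement rates).

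**What to change.** In the Statistical analysis section, replace the number five with at least 50 imputed datasets, for the primary outcome and for every other outcome that is imputed. Nothing else in the imputation model or the pooling needs to change. The cost is one number in the plan and a few minutes of computing. Patients, estimand and decision rules are unaffected.

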## Background

Insomnia disorder is prevalent (up to 66%) in patients with long-term medical conditions [1, 2]. Patients with a medical condition are 2.2 times more likely to have insomnia than patients without medical problems [3]. In DSM-5, insomnia disorder is defined as the complaint of poor sleep occurring at least 3 nights per week for at least 3 months with associated significant daytime effects [4]. Insomnia has been associated with an increased risk of various medical [5–7] and psychiatric disorders [8, 9] and injuries [10]. Sleep disorders in patients with medical conditions are assumed to negatively affect prognosis [11]. In patients with chronic illness, insomnia is independently associated with a significant decrease in overall quality of life [12]. The economic burden of insomnia in general is reported to be high. Health care use is reported to be twice as high among people with insomnia compared to those without, and insomnia-related work absence and reduced productivity are the main drivers of societal costs [13, 14]. Therefore, treatment of insomnia in patients with medical comorbidity is of utmost importance for health and functioning.

Insomnia treatments can be broadly divided into pharmacological (mainly benzodiazepine receptor agonists) and non-pharmacological. The European guideline for the diagnosis and treatment of insomnia recommends non-pharmacological treatment as first choice, of which cognitive behavioral therapy (CBT-I) is the most important one [15].

CBT-I is a multicomponent treatment package, applied face to face or online [15]. It includes behavioral and cognitive components, such as sleep hygiene education, stimulus control and sleep restriction interventions, relaxation techniques, and cognitive therapy. CBT-I has been found to improve sleep in about 70–80% of the participants both in individual and group treatment [16–19] and sustained effects were found on sleep and depression parameters [20]. A variety of studies have assessed the efficacy of CBT-I for insomnia comorbid with psychiatric and medical illness. Remarkably, the pre to post-treatment effect sizes in patients with comorbidities are comparable with those for primary insomnia and in some cases larger [21]. Furthermore, there is growing evidence that improved sleep following CBT-I positively influences the clinical course of the comorbid condition [22, 23].

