### Secondary objective

Secondary objectives include to evaluate 1) relapse in insomnia rates in both groups up to 12 months post treatment, 2) secondary outcomes after 12 weeks and 12 months of treatment (sleep quality, fatigue, pain, depression, anxiety, physical functioning, impairment of functioning), 3) treatment evaluation (side-effects, adherence and withdrawal), and 4) possible mediators and moderators of treatment outcome.

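### As most naturally read, the relapse comparison is made among week-12 responders, a group defined after randomisation; durability should also be compared in all randomised patients

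*Protocol article*

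**What the plan says.** The first item under Secondary objective is to evaluate "relapse in insomnia rates in both groups up to 12 months post treatment". The Statistical analysis section serves it with one sentence, under which "Percentages responders until relapse at 2, 4, 6, 8, 10, and 12 months post treatment in both treatment groups" are to be set against each other by survival analysis.

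Two definitions follow. The one for response reads: "Treatment response is defined as ≥ 8 point reduction on ISI". The one for relapse, which must be seen at two follow-up measurements in a row, reads: "A relapse is defined as a drawback of ≤ 8 points to the baseline score of the Insomnia Severity Index". The same paragraph also promises a summary by arm: "We will express the difference between amitriptyline and CBT-I in effect sizes and percentage responders".

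Intention-to-treat, meaning that "all randomized patients are included and are analyzed in their randomly assigned treatment group", is stated for the primary analysis. Intention-to-treat and per-protocol versions are also stated for the ANCOVAs and mixed models of the secondary outcomes. The relapse paragraph names no analysis set.

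**The concern.** Response is known only after treatment. If the survival curves start from responders, the two groups compared are no longer those formed by randomisation. Suppose one arm has fewer responders and they are mostly patients with a good outlook. That arm can then show fewer relapses even if the treatment does nothing to prevent relapse.

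Durability matters here because amitriptyline is stopped at 12 weeks. The mixed model of ISI covers weeks 6 and 12 only. The outcomes named for analysis at 12 months are sleep quality, fatigue, emotional complaints, functioning and pain; ISI is not among them. The relapse analysis is therefore the only described between-arm comparison of insomnia severity on the ISI after treatment ends. It could make an arm look more durable when fewer of its randomised patients have lasting benefit.

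**Working it through.** The protocol states no hazard ratio, event count, relapse rate or power for this comparison, so there is no figure to reproduce. The check has four steps.

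**1. Who is in the risk set?** The text does not say that only responders are included. Relapse, read as a return to within 8 points of baseline, is already satisfied on its threshold by anyone whose reduction is below 8. A non-responder therefore has no response to lose and cannot sensibly be at risk of relapse. This makes a risk set of responders the natural reading. That response is judged at week 12 is also inferred, from follow-up starting after treatment.

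**2. Identity.** Sustained response among all randomised = P(response) × [1 − P(relapse | response)]. With assumed values of 70% response and 30% relapse among responders for CBT-I, and 50% and 20% for amitriptyline:
- CBT-I: 0.70 × 0.70 = 49%
- amitriptyline: 0.50 × 0.80 = 40%

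The responder-only comparison favours amitriptyline (20% vs 30% relapse), while the all-randomised comparison favours CBT-I.

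**3. Size of the selection effect.** Assumed model: response and relapse are both probit outcomes that share a latent prognosis with loading λ, so the correlation between response and freedom from relapse is λ². Treatment has no effect on relapse. Response is 40% in one arm and 60% in the other. With a marginal relapse risk of 40%:

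| λ | Relapse among responders, 40% vs 60% arm | Spurious gap (points) | Sustained response, all randomised |
|---|---|---|---|
| 0.3 | 36.6% vs 37.8% | 1.2 | 25% vs 37% |
| 0.5 | 30.7% vs 33.7% | 3.0 | 28% vs 40% |
| 0.7 | 21.4% vs 27.1% | 5.7 | 31% vs 44% |

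With a marginal relapse risk of 30%, the gap is 1.0, 2.6 and 4.6 points for the same three loadings; with 35% it is 1.0, 2.8 and 5.2. The range is about 1 to 6 points.

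**4. A second model.** Here the latent prognosis drives both response and an exponential relapse hazard, again with no treatment effect on relapse. CBT-I response is set at 70%, the lower end of the Background figure ("CBT-I has been found to improve sleep in about 70–80% of the participants"), although improvement there need not mean an 8-point fall. The amitriptyline rate is assumed.
- 70% vs 70%: relapse among responders is identical in the two arms (34.5–38.8% in each).
- 70% vs 50%: spurious amitriptyline advantage of about 1 to 5 points; sustained response 43–46% vs 31–35%.
- 70% vs 40%: about 2 to 8 points; sustained response 43–46% vs 25–29%.

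**The case against.** **The denominator is not stated.** The sentence could mean the percentage of each whole treatment group still in response at each visit. That is close to the comparison proposed here, and the full protocol or analysis plan may say so. This stands as a limit: responder-only is the more natural reading, not a stated fact. The article does, however, fix the method, both definitions and the visits, and describes no comparison of lasting response in all randomised patients.

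**Response rates are reported alongside.** With the percentage of responders per arm, a reader could apply the identity in step 2 and notice fewer lasting responders. This is a real but partial mitigation, since it yields no planned between-arm estimate with a confidence interval.

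**The effect is small against noise.** With 95 per arm, response of 40% and 60% leaves 38 and 57 responders. For 21% vs 27% relapse, the standard error is √(0.21×0.79/38 + 0.27×0.73/57) ≈ 0.088, about 9 points, with roughly 10% power at two-sided 5%. A significant result from this bias alone is unlikely. That is correct, but the point estimate and the curves would still be distorted.

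**Relapse after response is a legitimate question**, and other outcomes are compared at 12 months by randomised arm. Both points hold. They support keeping the responder curves as description, but do not turn them into a randomised comparison of ISI durability.

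**A stronger reading.** A reader might infer that the curves will favour amitriptyline. The documents do not support this. They give no amitriptyline response rate, and the trial hypothesises non-inferiority rather than a response deficit. The direction also depends on responders in the lower-response arm having the better prognosis.

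**Conclusion.** The point holds in limited form. On its most natural reading, the relapse analysis compares groups selected after randomisation, so a difference between arms cannot be attributed to treatment alone. The spurious gap is about 1 to 6 points at 40% vs 60% response. This rests on assumed response rates, a marginal relapse risk of 30–40%, loadings of 0.3 to 0.7 and no treatment effect on relapse. It is zero when response rates and responder mix are equal, and it could run the other way under a different selection pattern. The matter concerns the first-listed secondary objective; a reader should not extend it to the week-12 primary analysis, which includes all randomised patients.

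**What to change.** State the denominator of the relapse analysis, and make the between-arm durability comparison on all randomised patients in one of two ways:
- sustained response at 12 months (responder at week 12 and no relapse), reported as a risk difference with a confidence interval; or
- time to failure, with week-12 non-responders counted as failures at time zero.

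Keep the responder-only survival curves, labelled as descriptive. Because a reduction of exactly 8 points meets both the response and the relapse threshold as written, the combined endpoint also needs definitions that do not overlap.

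The cost is a change of wording and one analysis on ISI data already being collected. Non-responders may be offered further treatment outside the study; counting them as failures at week 12 keeps that later treatment from changing their status. The downside is that the estimate combines response and relapse, so the two components should be shown beside it.

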### Participants

Patients known with a long-term medical condition, aged 18–85 years old, suffering from insomnia disorder meeting DSM-5 criteria, and scoring ≥ 10 on the Insomnia Severity Index (ISI) [41] are eligible for participation [42]. A long-term chronic medical condition refers to all long-term medical conditions and/or persistent physical complaints (> 3 months) that require medical attention (in the form of consultation in medical health care, medication, aid or treatment) that cause dysfunction, discomfort, or social problems. The upper age limit is conform the guideline for low-dose amitriptyline treatment of neuropathic pain and the Food and Drug Administration approved use of doxepin (a sedating tricyclic antidepressant as well) in the treatment of insomnia. The DSM-5 criteria for insomnia disorder are sleep problems in at least 3 nights a week, for at least 3 months with consequences for daytime functioning, and the sleep problem cannot be better explained by or occurs exclusively during the course of another sleep disorder.

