### Outcome measures

Primary outcome is insomnia severity measured with the Insomnia Severity Index (ISI) [41] after 12 weeks of treatment. The ISI is a 7-item questionnaire scored on a 5-point Likert scale reflecting the severity of both nighttime and daytime aspects of insomnia disorder as perceived by the participant in the last 2 weeks. Total scores range from 0 (no insomnia) to 28 (severe insomnia). A score of ≥ 10 is used to define clinical insomnia [44] .

We will use the Consensus sleep diary [45] for 1 week. Several variables will be calculated from the sleep diary: sleep efficiency (SE; percentage of time slept from the total amount of time spent in bed), sleep onset latency (SOL; time it takes to first fall asleep), number of awakenings (NOA), and total sleep time (TST, total number of hours the participant has slept). All these estimates are registered for 7 nights and for each variable a mean score over 7 days will be calculated.

Fatigue will be assessed with the subscale Fatigue severity of the Checklist Individual Strength (CIS-20), indicating the level of fatigue in the previous 2 weeks, measured with 8 items on a seven-point scale (range 8–56). A score of 35 or higher on the subscale indicates severe fatigue [46].

Anxiety and depression will be assessed with the Hospital Anxiety and Depression Scale (HADS) [47, 48], which has been extensively used in patients with medical conditions. The HADS contains 14 items (7 on depression and 7 on anxiety). A total score (range of 0–21) for each subscale is computed.

Pain severity and impact of pain on functioning will be measured with the 2-item subscale Bodily pain of the Short-Form 36-item Health Survey (SF-36) [49]. A total score is calculated ranging from 0 to 100. Higher scores indicate less pain and less impact of pain on functioning [50].

Impairment of functioning is assessed with the Work and Social Adjustment Scale (WSAS) [51]. The WSAS assesses five domains of functioning (work, home management, social leisure activities, private leisure activities, close relationships) with one item each. Each item is scored on an 8-point Likert scale. The usual timeframe (1 year) is adjusted to the past 2 weeks.

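### The relapse definition overlaps the response definition at exactly 8 ISI points, so a stable responder can be counted as relapsed without any worsening

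*Protocol article*

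**What the plan says.** The protocol article, Statistical analysis, gives the two rules in adjacent sentences. The first is "Treatment response is defined as ≥ 8 point reduction on ISI". The second makes relapse a drawback with an upper limit (≤) of 8, expressed in "points to the baseline score of the Insomnia Severity Index measured during follow-up at two subsequent measurements". Responders remaining free of relapse at 2, 4, 6, 8, 10 and 12 months post treatment are to be compared between arms by survival analysis. Relapse up to 12 months is the first item under Secondary objective.

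Two other places bear on the rule. Outcome measures states: "A score of ≥ 10 is used to define clinical insomnia". Participants sets the same value for entry: "scoring ≥ 10 on the Insomnia Severity Index (ISI").

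The relapse sentence requires neither a minimum worsening from the end-of-treatment score nor an absolute ISI level.

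**The concern.** Both rules are anchored to baseline and both include the value 8. The state that qualifies a patient as a responder can therefore, if it simply persists, qualify the same patient as relapsed. There is no gap between the two rules, so ordinary visit-to-visit variation near the threshold can produce events.

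The wording is also unclear about direction. Read literally, as a worsening of at most 8 points, it would count small rises and leave out large rebounds.

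Amitriptyline is stopped at 12 weeks (Interventions, Medication), so the relapse comparison speaks directly to durability after stopping. If part of the event count comes from the definition, the relapse curves overstate loss of response.

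**Working it through.** The protocol states no relapse rate, event count or power for this endpoint, so there is no figure to reproduce. The first three steps need only the protocol's rules.

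**1. Overlap.** Let b be the baseline ISI and x a later ISI.
- Response: b − x ≥ 8, so x ≤ b − 8.
- Relapse (return to within 8 points of baseline): b − x ≤ 8, so x ≥ b − 8, at two consecutive follow-ups.
- Both hold at x = b − 8, for every baseline. With b = 18, ISI 10 at week 12 is a response, and ISI 10 at two follow-ups is a relapse: change 0.
- With a 9-point reduction (b = 18, week-12 ISI 9), follow-up scores of 10 and 10 are a relapse: change +1, sustained.

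**2. Position against the cut-off of 10.** The relapse threshold is b − 8.

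| Baseline | Relapse possible from ISI |
|---|---|
| 10 | 2 |
| 12 | 4 |
| 14 | 6 |
| 15 | 7 |
| 17 | 9 |
| 18 | 10 |

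Baselines 10 to 17 allow relapse below 10; from 18 upward they do not. Example: baseline 14, week-12 score 5 (reduction 9), follow-ups 6 and 6 (reduction 8) is a relapse.

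**3. Literal reading.** If relapse meant a worsening of at most 8 points, a 1-point rise would count and a 10-point rebound would not (for example baseline 22, week 12 ISI 8, follow-up 18).

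**4. Size, by simulation.** All inputs here are assumptions. Baseline mean 18, SD 4, entry at ISI ≥ 10; reduction mean 8, SD 4.4 (the protocol's 4.4 is the SD of the ISI, used here for the reduction); visit noise SD 2; integer scores; six follow-ups; two consecutive visits required; no true change after week 12.

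| Relapse rule | All observed responders | Responders with true reduction ≥ 8 |
|---|---|---|
| Reduction ≤ 8 (as written) | about 30% | about 17% |
| Reduction < 8 | about 19% | about 7% |
| Reduction < 8 and ISI ≥ 10 | about 14% | about 5% |

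- About 15% of observed responders sit at exactly 8 points at week 12.
- About 53% of the as-written relapses are in patients whose true reduction was below 8: 0.53 × 30 ≈ 16 of the 30 points. They passed the response rule on a favourable week-12 score and then regressed to the mean.
- The effect of the inequality is 30 − 19 = 11 points in all responders and 17 − 7 = 10 points in those with a true reduction of at least 8.

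**5. Sensitivity.** Across noise SD 1.5 to 2.5 and mean reduction 7 to 10, the as-written rate is 18% to 39%. With mean reduction 12 and noise SD 2 it is about 13%. A second set of assumptions (ISI SD 4.4, test-retest reliability 0.7 to 0.9, mean baseline 15 to 20, mean reduction 8 with SD 5) gives 22% to 27% as written and 12% to 19% with the strict inequality.

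**The case against.** **The confirmation requirement is a real safeguard.** Nobody is relapsed at week 12, and a single high score is not enough. This stands: no patient is responder and relapsed at the same visit. It does not cure the overlap, because a patient who stays at exactly 8 points below baseline satisfies the confirmation too.

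**The overlap is one integer value.** True. The lack of any gap between the rules matters more than the shared value itself.

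**A reader might infer that the whole 30% is produced by the relapse rule.** It is not. Roughly half is regression to the mean after selection on a noisy week-12 score, which any threshold would show.

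**A reader might infer that relapses are typically declared far below the insomnia cut-off.** That fits only the lower part of the 10 to 17 range. For baselines 15 to 17 the threshold is 7 to 9, at 18 it is 10, and the protocol gives no baseline mean, so the share affected is unknown.

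**A reader might infer that the rule biases the arm comparison.** With no true relapse, arms with mean reductions of 7 and 10 would show about 35% and 21% relapsed as written. Even with reduction < 8 plus ISI ≥ 10 they would show about 17% and 9%. The gap shrinks from about 14 to 8 points but does not vanish, and nothing in the protocol shows which arm, if either, would be disfavoured.

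**A baseline-anchored relapse rule is legitimate.** It mirrors the response rule, and the protocol uses 10 for entry and clinical insomnia, not for relapse. Requiring ISI ≥ 10 would also mean that a responder with baseline 10 must return fully to baseline. That requirement is a design option, not an error correction.

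**Conclusion.** Wrong as written. The collision at exactly 8 points follows from the two stated rules and needs no assumption, and the sentence fails on the literal reading as well. The possibility of relapse below ISI 10 for baselines 10 to 17 is equally certain; its frequency is not known.

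Under the assumptions shown, changing the inequality alone lowers spurious relapse by roughly 10 to 11 percentage points. That size depends on the assumed baseline, reduction and noise, and is smaller when responders sit well beyond the threshold.

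The point concerns one secondary endpoint, and relapse is not the only evidence on durability, since 12-month analyses of the secondary outcomes are also planned. The primary week-12 comparison is unaffected.

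**What to change.** Replace the relapse sentence with: *Relapse = in a week-12 responder, an ISI reduction from baseline of less than 8 points at two consecutive follow-up assessments.* This states the direction and removes the overlap.

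Add a sensitivity analysis that also requires ISI ≥ 10 at both assessments. It is needed to address relapse below the cut-off: the strict inequality moves the threshold only to b − 7, which is still under 10 for baselines 10 to 16.

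The cost is one sentence plus one sensitivity analysis, on data already being collected. The downside is fewer relapse events and somewhat wider intervals.

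Concomitant care during the trial offers further treatment to participants who relapse, without saying whether the ISI rule determines this. The two sections should be reconciled; this point takes no position on that clinical decision.
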